## Abstract

**Background:**

Socioeconomically disadvantaged adults are both more likely to be obese and have lower levels of health literacy. Our trial evaluates the implementation and effectiveness of primary care nurses acting as prevention navigators to support obese patients with low health literacy to lose weight.

**Methods/Design:**

A pragmatic cluster randomised trial will be conducted. Twenty practices in socioeconomically deprived areas, 10 each in Sydney and Adelaide, will be recruited and randomised to intervention and control groups. Twenty to 40 eligible obese patients aged 40–70 years with a BMI ≥ 30 kg/m^2^ and with low health literacy will be enrolled per practice. The intervention is based on the ‘5As’ of the chronic disease model approach – Assess, Advise, Agree, Assist and Arrange – and the recommendations of the 2013 *Clinical practice guidelines for the management of overweight and obesity in adults*, *adolescents and children in Australia*. In the intervention practices, patients will be invited to attend a health check with the prevention navigator who will assess the patient’s risk and provide brief advice, assistance with goal setting and referral navigation. Provider training and educational meetings will be held. The providers’ attitudes to obesity, confidence in treating obesity and preventive care they provide to obese people with low health literacy will be evaluated through questionnaires and interviews. Patients’ self-assessment of lifestyle risk factors, perception of preventive care received in general practice, health-related quality of life, and health literacy will be assessed in telephone interviews. Patients’ anthropometric measures will be recorded and their health service usage will be determined via linkage to the Australian government-held medical and pharmaceutical data.

**Discussion:**

Our trial will provide evidence for the effectiveness of practice nurses as prevention navigators to support better weight management for obese patients with low health literacy.

**Trial registration:**

This trial is registered with the Australian New Zealand Clinical Trials Registry (ACTRN12614001021662). Date registered 24/09/2014.

## Background

In Australia, obesity is one of the most significant problems facing the healthcare system, with 63% of the population classified as overweight/obese (body mass index [BMI] 25 kg/m^2^ or more) [1]. Obesity is more prevalent among disadvantaged socioeconomic groups than the rest of the population [2].

Obesity is common (27%) among patients presenting in Australian general practice [3]. The ‘5As’ model (Assess, Advise, Agree, Assist and Arrange) provides a framework for preventive care in primary care [4-6]. Providing interventions across the 5As has been advocated in weight management [7-10] and has been shown to increase patient motivation to change their diet behavior [11]. The Australian National Health and Medical Research Council’s *Clinical practice guidelines for the management of overweight and obesity in adults, adolescents and children in Australia* (*the Guidelines*) make recommendations for obesity management in clinical practice across each of the 5As [2]. However, there is evidence that general practitioners (GPs) do not adequately implement these recommendations: a pilot study assessing preventive care for primary care patients with low health literacy found only 15 and 7% of patients in the age group 40–69 years with BMI and waist circumference recorded, respectively [12]. Another study has found low rates of lifestyle advice and referral [13]. These gaps in performance have been attributed to a variety of patient, provider, practice and system factors [14,15].

Health literacy is the capacity to obtain, process, and understand basic health information and services needed to make appropriate health decisions [16]. People with low health literacy are more likely to suffer higher chronic disease morbidity and mortality [17,18] and less likely to receive preventive care [19]. Over 20% of the Australian population has very low health literacy and this is more prevalent among those from disadvantaged socioeconomic backgrounds [20].

Nurses have potential to help adult patients improve health behaviours [21] and to deliver interventions for obesity management in general practice [22]. The feasibility of practice nurses (PNs) in obesity prevention and management has been demonstrated in Australian general practice [23,24]. The objective of our trial is to evaluate the implementation and effectiveness of using PNs in the role of ‘prevention navigators’ to support obese patients with low health literacy to better manage their weight.

### Hypotheses

#### Primary hypotheses

PNs acting as prevention navigators in intervention practices will demonstrate greater improvement in their self-reported behaviour and confidence in assessing obese patients with low health literacy and providing advice and referral to them for weight loss compared with PNs in the control group.Recruited patients (obese patients with low health literacy) attending intervention practices will be, at six months, more likely to report having (i) received assessment, advice and referral for weight loss and (ii) attended/used community-based weight loss lifestyle modification programs to which they have been referred to compared with patients in control practices.Recruited patients attending intervention practices will be, at 12 months, more likely to have improved their health literacy related to weight loss than patients in control practices.

### Secondary hypotheses

Recruited patients attending intervention practices will be, at 12 months, more likely to have (i) increased intake of dietary portions of fruit and vegetables per day and minutes of moderate and/or vigorous intensity physical activity per week, (ii) reduced consumption of high fat food and hours of sedentary activity per day, and (iii) moderated alcohol consumption compared with patients attending control practices.Recruited patients attending intervention practices will be, at 12 months, more likely to (i) have reduced their baseline weight by 5% or maintained it and (ii) report improvements in their health-related quality of life compared with patients attending control practices.The total cost of health service use of patients in the intervention and control practices will not be different.GPs in intervention practices will demonstrate greater improvement in their self-reported behaviour and confidence in assessing obese patients with low health literacy and providing advice and referral to them for weight loss compared with GPs in the control group.

## Methods/Design

### Research design

A pragmatic cluster-randomised controlled trial will be conducted with randomisation of practices to intervention and control groups. Randomisation will be in permutated blocks and will occur across the two cities. Due to the nature of the intervention, participating GPs and PNs will not be blinded to the intervention.

### Timeline

The intervention will be delivered over a period of 6 months.

### Trial participants

#### General practices

The South Western Sydney and Central Adelaide and Hills Medicare Locals will assist the research team to identify eligible practices. The eligibility criteria include practices being situated in low socioeconomic areas, having electronic medical records that can be audited and with at least one consenting GP and PN each. Practices will be emailed or faxed a synopsis of the trial protocol and invited to participate. Non-responding practices will be contacted by telephone. Once a practice has indicated a willingness to participate, the research team will visit the practice and explain the trial to the interested GPs and PNs. Twenty practices will be recruited, 10 each in Sydney and Adelaide.

#### Patients

The patient eligibility assessment and recruitment will be conducted over a 4 week period. During this period, posters will be displayed in the waiting room informing patients of practice participation in the trial. The patient eligibility assessment will be carried out in 2 steps:Software, specifically developed for this trial, will be installed on the reception computer(s). The software will identify which patients scheduled to visit in each session are potentially eligible to participate. The eligibility criteria include: aged 40–70 years, at least one practice attendance in the previous 12 months, and the GP the patient usually attends being a trial participant. The software will exclude patients who have the following: heart disease, stroke, insulin-treated diabetes, and chronic renal impairment (eGFR < 60 mls/minute/1.73 m^2^). Patients having current treatment with a weight loss medication (orlistat or phentermine) and previous or planned bariatric surgery in the next 12 months will also be excluded.For each eligible patient the software will print an enrollment form, which includes four parts: (i) a health literacy screening questionnaire, (ii) an eligibility-determining data form, (iii) a patient consent form, and (iv) a pre-filled clinical data form. The receptionist will hand out the enrollment form together with the patient information sheet and ask the patient to complete the first part (health literacy screening questionnaire) in the waiting room. Patients who have insufficient proficiency in the English language but can complete the screening questionnaire in a language for which a translated questionnaire and patient information sheet are available, will receive the forms translated into their own language.The screening questionnaire will contain a slightly modified version of the three questions developed by Chew *et al.* (Table 1) [25]. These have been used in our own pilot study [12] and in other studies with disadvantaged populations [26,27]. A fourth question will assess patients’ language preference for reading medical or health care instructions [28]. To encourage inviting all potentially eligible patients in the screening survey, the reception staff will receive a $200 gift voucher.

**Table 1 Tab1:** **Health literacy screening questionnaire**

A. How often do you have someone help you read health information materials?	1. Never
	2. Occasionally
	3. Sometimes
	4. Often
	5. Always
B. How often do you have problems learning about your medical condition because of difficulty understanding health information materials?	1. Never
	2. Occasionally
	3. Sometimes
	4. Often
	5. Always
C. How confident are you filling in medical forms by yourself?	1. Extremely
	2. Quite a bit
	3. Somewhat
	4. A little bit
	5. Not at all
D. In which language do you prefer to read your health care information?	English
	OtherGPs will score the completed health literacy screening questionnaire, fill in the eligibility-determining data form, and assess the overall patient eligibility. The patient will be considered eligible if the combined score of the three health literacy questions is >10 [27] or the score of the question *“How confident are you filling in medical forms by yourself?”* is ≥3 [25] and the patient has a BMI ≥30 kg/m^2^, is willing to return for a health check (only in intervention practices), and does not have any of the exclusion criteria.

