### Intervention description

The intervention has two parts: a clinical intervention and a practice-level intervention.

Clinical intervention: This will be delivered over a 6-month period by GPs and PNs acting as prevention navigators. As recommended by *the Guidelines,* other guidelines and other research, the clinical intervention is based on the 5As framework [2,4,5,7], comprising: (i) Assessment of health literacy, obesity, dietary habits, physical activity levels and readiness to change (ii) Advice on risk of being overweight and lifestyle changes (iii) Agreement on realistic weight loss, diet and physical activity goals (iv) Assisting by referral to services and/or programs and (v) Arranging follow-up telephone calls and visits to review progress. Steps i-iv will be delivered at a health check visit about 2 weeks after the health literacy screening and enrollment of patients in the trial (Figure 1).

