#### Evaluation of patients

All patients will be surveyed at baseline, 6 and 12 months. In the intervention group, a subsample of Arabic and English-speaking patients will also be interviewed at baseline and 12 months. Data on anthropometric measures will be collected at baseline and 12 months.Patient Surveys: A questionnaire will be administered by telephone in English or in the language in which patients completed the health literacy screening questionnaire. The survey used at baseline and 12 months includes the following five sections:i.Assessment of lifestyle-related risk factors and management by primary healthcare providers and patient’s stage of change.ii.The 12-item short form – the SF-12® Health Survey – with a 4-week recall to measure eight health-related quality of life domains: physical functioning; role-physical; bodily pain; general health; vitality; social functioning; role-emotional; and mental health [34].iii.Health Literacy Questionnaire to assess patients’ general health literacy needs and challenges. This questionnaire covers nine conceptually distinct areas of health literacy that capture a wide range of the lived experiences of people attempting to engage in understanding, accessing and using health information and health services [35]. The domains are: feeling understood and supported by healthcare providers; having sufficient information to manage my health; actively managing my health; social support for health; appraisal of health information; ability to actively engage with healthcare providers; navigating the healthcare system; ability to find good quality health information; and understanding health information well enough to know what to do.iv.Impact of Weight on Quality of Life-Lite (IWQOL-Lite) [36], a validated, 31-item, self-report tool, to measure obesity-specific quality of life. In addition to a total score, there are scores on five domains: physical function; self-esteem; sexual life; public distress; and work.v.Demographic questions such as age, sex, and country of birth.At 6 months, patients will be administered a shortened version of the survey covering only assessment and management of lifestyle-related risk factors and stage of change.Patient Interviews: A subsample of Arabic and English-speaking patients, in the intervention group, will be qualitatively interviewed over telephone. The aim for this interview is to explore ethnicity-related factors which influence health literacy for weight management.Anthropometric Measures: At baseline, at the time of patient enrollment, GPs will check patient weight and height and calculate BMI. This information will be recorded on the enrollment form. At 12 months, the research team will send invitation letters to patients to attend their practice for final data collection. After two weeks, reminders will be sent to patients who have not responded to the initial invitation. At this visit, data will be collected on weight, BMI and current use of medicines which could impact body weight.

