### Trial status

The trial is registered with the Australian Clinical Trials Registry ACTRN12614001021662.

The trial is underway with baseline data collection completed and the intervention commenced.

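### Willingness to return for a health check is an entry criterion in intervention practices only, so the patient-level comparisons between arms are open to selection bias

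*Protocol article*

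**What the plan says.** The text beneath Table 1 (Patients section of the protocol article) sets out who may enter. A patient needs a qualifying health literacy score and a BMI of at least 30, and must be someone who "is willing to return for a health check (only in intervention practices), and does not have any of the exclusion criteria". The willingness criterion is the only one in that list that depends on the arm.

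The same text has the GPs "score the completed health literacy screening questionnaire, fill in the eligibility-determining data form, and assess the overall patient eligibility". Under Research design there is "randomisation of practices to intervention and control groups", and "participating GPs and PNs will not be blinded to the intervention". The Intervention description places the health check "about 2 weeks after the health literacy screening and enrollment of patients in the trial", so willingness is judged at entry, before anything is delivered.

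The analysis paragraph after Table 2 offers three general safeguards: a comparison of change with adjustment for baseline imbalance, multiple imputation, and analysis by intention to treat. It names no covariate. The baseline telephone survey for all patients includes "Assessment of lifestyle-related risk factors and management by primary healthcare providers and patient’s stage of change". Trial status reports: "The trial is underway with baseline data collection completed and the intervention commenced".

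**The concern.** Randomising practices makes the two arms' patients comparable in expectation only if both arms admit patients by the same rule. Here they do not. The intervention arm is filtered for patients prepared to make an extra visit about their weight, and the control arm is not.

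The article does not state the order of randomisation and recruitment. A criterion used only in intervention practices, however, can be applied only if the GP knows the practice's allocation when judging eligibility.

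Willingness to return is a plausible marker of motivation. Patients who have it may be more likely to attend a community programme, change diet and activity, and lose weight, whether or not the intervention works. Programme attendance belongs to a primary hypothesis; behaviour and weight belong to secondary ones. At stake is whether a difference between arms can be credited to the prevention navigators rather than to who was let in.

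**Working it through.** **Step 1: follow one patient through the rule.** Take a patient aged 40–70 with BMI of at least 30, low health literacy and no exclusion, who would consent to the study but would not come back for a health check.

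- In an intervention practice the willingness criterion applies, and the patient is not enrolled.
- In a control practice it does not apply, and the patient is enrolled.

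**Step 2: expected difference with no true effect.** Let q be the share of such patients among those who would otherwise consent, and D the mean outcome of willing patients minus that of unwilling patients (M_w − M_u).

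- Intervention arm mean: M_w
- Control arm mean: (1 − q) M_w + q M_u
- Difference: q (M_w − M_u) = q × D

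Neither q nor D is in the article, so both are assumptions. The article states no figure on this point that could be reproduced.

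**Step 3: range for a proportion.** With q = 10–40% and D = 10–30 points:

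- lowest: 0.10 × 10 = 1 point
- highest: 0.40 × 30 = 12 points

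Table 2 plans on a difference of 25 points for advice and for referral or attendance.

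**Step 4: what this does to the error rate (illustration only).** Inputs from the article are 20 practices, 30 patients per practice (Table 2), 20% loss, two-sided 5% level, and ICCs of 0.014 (health literacy score) and 0.051 (advice on diet). Added assumptions are 10 practices per arm, a control proportion of 30%, and D as shown. The ICCs serve only to set the precision; no direction is implied for those two outcomes.

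Followed up per arm: 10 × 30 × 0.8 = 240, or 24 per practice. Effective size is 240 / (1 + 23 × ICC):

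- ICC 0.014: 240 / 1.322 = 181.5
- ICC 0.051: 240 / 2.173 = 110.4

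| q | Score, D = 0.4 SD: bias | False-positive rate (nominal 5%, two-sided) | Proportion, D = 20 points: bias | False-positive rate in favour of intervention (nominal 2.5%) |
|---|---|---|---|---|
| 10% | 0.04 SD | 6.7% | 2 points | 5.1% |
| 20% | 0.08 SD | 11.9% | 4 points | 9.3% |
| 30% | 0.12 SD | 20.8% | 6 points | 15.5% |
| 40% | 0.16 SD | 33.2% | 8 points | 24.0% |

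All of this is before baseline adjustment. With q = 0 or D = 0 the nominal level holds. A larger sample would not shrink the bias.

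**Step 5: set the stated safeguards against the problem.**

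- Intention to treat keeps enrolled patients in their arm. The unwilling patients of intervention practices were never enrolled.
- Multiple imputation fills in values for enrolled patients, not for people who never entered.
- Baseline adjustment acts on the right imbalance, but only on what is measured and entered in the model. No motivation variable is named.

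**The case against.** The best case on the other side has four parts.

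*Control patients are selected too.* Everyone gives written consent, accepts three telephone surveys and is invited back to the practice at 12 months. This stands: q must mean the extra refusal among people who would otherwise join, and the upper end of 10–40% has no anchor in the article. At 10–20% the distortion is real but modest.

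*Baseline adjustment is already planned.* This stands in part. It may remove some of the bias, and the figures above take no credit for it. As worded, it does not commit the analysis to any measure of motivation.

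*The direction is not general.* This also stands. A reader might infer that every patient-level comparison is biased towards the intervention, but the article does not support that. No clear argument gives a direction for health literacy. The cost hypothesis is one of no difference, and more willing attenders could raise service use and work against it. Nurse and GP outcomes do not depend on this criterion.

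*Reported assessment, advice and referral are different.* A reader might argue that these are inflated because they are delivered at the health check. That delivery is the intervention itself, not selection in the absence of an effect. Leaving out unwilling patients there removes dilution of a real effect, which is a separate matter.

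None of this restores equal entry rules in the two arms.

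**Conclusion.** The concern holds in this form: an explicit, arm-specific entry criterion, applied by GPs who know the allocation, leaves the patient-level comparisons open to selection bias. The existence of the rule is certain from the text; the size of its effect is not. On the assumed ranges it is 1–12 points against a planned 25, before adjustment, and nil if few patients refuse or if those who refuse have similar outcomes. A direction favouring the intervention is plausible for programme attendance, lifestyle behaviour and weight, and is not established beyond these.

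Two tempting remedies fail. Deleting the clause now cannot change who was enrolled. Limiting the claim to patients willing to attend does not repair the comparison either, because the control arm still contains unwilling patients.

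**What to change.** The criterion should have been the same in both arms. With baseline collection complete, three changes remain open and should be fixed before outcomes are analysed.

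1. Pre-specify baseline stage of change, baseline BMI and the baseline value of the outcome (where measured) as fixed covariates in every patient-level model. Use stage of change only if it was measured before the health check; the text does not give the order of the baseline survey and that visit. It is in any case an imperfect proxy for willingness.
2. Report, by practice and arm, the numbers screened, eligible, excluded solely as unwilling, and enrolled, as far as the retained forms record the reason. The article does not say whether they do. These counts would put a figure on refusal in the intervention arm.
3. State the arm-specific criterion and the residual confounding as a limit on the causal conclusion for patient outcomes.

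The cost is analysis-plan wording, a named motivation covariate, and a count from forms if they allow it. The downside is that confounding by unmeasured motivation will remain after adjustment.
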